### Supportive pilot data

Feasibility and acceptability of the randomized control behavioral trial (RCT) procedures and the breastfeeding self-efficacy intervention (BSEI) were determined in a single-center pilot RCT conducted between February 2019 and November 2020, entitled Breastfeeding and blood Pressure patterns in MOthers with recent hypertensive coMplications of pregnancy (BP-MOM study, ISRCTN.com, # 18352227, registered on Jan 29, 2019). Of 183 individuals with HDP screened for study eligibility, 90 met the inclusion criteria and were approached. Of these, 45 agreed to participate, completed baseline measures and were randomized to usual care (*N* = 21) or the BSEI (*N* = 24) [79]. Follow-up to the 6-month clinic appointment was completed by 37 (82%) participants. Follow-up to 12 months was interrupted by the first wave of the COVID-19 pandemic, and was conducted predominately remotely due to public health restrictions (*N* = 27, 80% completed remote and *N* = 7, 20% completed in person 12-month follow-up).

Mean systolic BP was lower at all time-points in the intervention group than the usual postpartum care group (Table 1), as was number with BP in the hypertensive range, and number requiring anti-hypertensive therapy (Fig. 2).

**Table 1 Tab1:** BP-MOM mean systolic and diastolic blood pressure at each time point in postpartum women with HDP

	Total	Breastfeeding Intervention	Usual Postpartum Care	*p*-value
N	45	24	21	
Baseline systolic (m, sd)	129 (11.3)	127 (11.8)	132 (10.5)	.29
Baseline diastolic (m, sd)	82 (8.9)	80 (10.3)	85 (6.0)	.11
N	36	18	18	
3-month systolic (m, sd)	115 (12.1)	115 (11.9)	116 (12.5)	.77
3-month diastolic (m, sd)	74 (8.4)	72 (8.3)	75 (8.4)	.29
N^a^	31	15	16	
6-month systolic (m, sd)	113 (11)	112 (12.3)	114 (10)	.70
6-month diastolic (m, sd)	72 (10.2)	71 (11.7)	73 (8.7)	.56
N^b^	29	13	16	
12-month systolic (m, sd)	118 (13)	117 (10.1)	119 (15.3)	.75
12-month diastolic (m, sd)	76 (9.6)	77 (9.8)	76 (9.7)	.61

^a^ Data at 6-month time point does not reflect full sample size as in-person visits were limited due to the COVID-19 pandemic. ^b^ Blood pressure values at 12-months were derived from both home blood pressure measurements (self-reported) and in person automated office blood pressure measurements due to restrictions for in-person visits during the COVID-19 pandemic

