### Study outcomes

Our primary study endpoint is average systolic and/or diastolic BP, in mmHg, measured by standard recommended technique using validated automated office blood pressure devices. In the case of home blood pressure, an average of four daily measurements over a one-week period is used, after discarding the first day of measurement. Blood pressure data is collected at baseline, 6 weeks, 3 months, 6 months, and 12 months postpartum with the primary outcome at 12 months with repeat blood pressure and other cardiometabolic markers, as well as novel biomarkers. The purpose of the latter measurement is a secondary aim of sheMATTERS, which is enhanced cardiovascular phenotyping of those with HDP.

Our secondary study endpoint includes 1) elevated blood pressure (displayed automated mean blood pressure > 135 mmHg systolic and/or > 85 mmHg diastolic) or use of/increase in previous use of antihypertensive drug therapy, and 2) the presence of metabolic syndrome [83]. An additional secondary endpoint is systolic and/or diastolic blood pressure at 6months postpartum.

Breastfeeding outcomes include the duration of exclusive breastfeeding (in weeks), total breastfeeding duration (in weeks), the proportion of participants exclusively breastfeeding at 6 months, and the proportion of participants continuing any breastfeeding at 6 months and 12 months. Given high rates of in-hospital formula supplementation of breastfeeding infants born to persons with HDP [50], we have defined exclusive breastfeeding as the provision of nothing but breastmilk (either at the breast or via milk expression) after the first 7 days of life.

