### Sample size calculation

In order to detect a 5 mmHg between-group differences in postpartum blood pressure and in breastfeeding rates, we are aiming to recruit an approximate of 323 participants (after accounting for a 30% loss to follow-up). Around 278 of these participants (86%) will be randomized to either the breastfeeding intervention group or breastfeeding control group, and 45 participants (14%) who will not be breastfeeding will serve as a comparison group in the observational arm of the study. Accounting for annual delivery rates at each of the study sites and assuming that ~ 8% of deliveries are affected by HDP at all sites, and 70% of those will initiate breastfeeding (an average of general Canadian population initiation rate of ~ 90%, German HDP population rate of 40%, and United States rate of 82% in those with HDP) [48, 94] we anticipated reaching our recruitment target over a two-year period, without accounting for additional recruitment delays due to the pandemic.

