### Statistical analysis

Descriptive statistics will be used to characterize the study population. We will compare baseline characteristics in the experimental study arms to assess randomization effectiveness. We will assume two-sample tests such as chi-square tests, t-tests, and non-parametric tests as appropriate to assess between-group differences in various characteristics and outcome measurements. They include proportion on antihypertensive drug therapy, proportion of EBF at 6 months, total breastfeeding duration in weeks, total EBF in weeks, metabolic syndrome, as well as differences in physical activity and dietary patterns. Differences in the primary outcome between the intervention and control groups on study outcomes will be assessed using an intent-to-treat approach. To examine the effect of BSEI on systolic and/or diastolic BP at 12 months, we will use generalized linear regression (GLM) to model for continuous BP readings and the Generalized Estimating Equation (GEE) analyses using logistic regression (reduction of 5 mm in SBP from the baseline vs. no change). We will calculate beta estimates with 95% confidence intervals (CIs) after adjusting for any observed between group differences despite randomization. Given that we plan to recruit non-breastfeeding parents (*N* = 45), we will model breastfeeding first as a continuous exposure variable (number of weeks) with systolic BP as the outcome in a multivariable linear regression model. We will also evaluate the dose-response of breastfeeding categories (i.e., none, < 3 months, < 6 months, > 6 months) to determine systolic and diastolic BP trajectories. In a sensitivity analysis, we will use different combinations of systolic blood pressure and diastolic blood pressure, and delta change in BP from baseline will be assessed. Breastfeeding duration will be divided into quintiles/quartiles, and those will be correlated with a series of BP measures. We will also perform a survival analysis modeling time to cessation of exclusive breastfeeding in both study groups. The model will incorporate interval censoring and compare differences between groups controlling for variables of interest, such as baseline self-efficacy score, maternal education, income, and age. Kaplan-Meir curves and cox-regression will be used to address these aspects.

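### As written, the named 12-month regression omits randomised women without a 12-month blood pressure and leaves their interim readings unused, although the plan allows for 30% loss

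*Protocol article*

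**What the plan says.** - **Outcome and visits** (Study outcomes): "Blood pressure data is collected at baseline, 6 weeks, 3 months, 6 months, and 12 months postpartum with the primary outcome at 12 months".
- **Expected loss** (Sample size calculation): the target of 323 recruits is set "after accounting for a 30% loss to follow-up". Of these, "Around 278 of these participants (86%) will be randomized to either the breastfeeding intervention group or breastfeeding control group".
- **Target difference** (same section): "In order to detect a 5 mmHg between-group differences in postpartum blood pressure".
- **Primary model** (Statistical analysis): the between-arm comparison is labelled intent-to-treat, and then "To examine the effect of BSEI on systolic and/or diastolic BP at 12 months, we will use generalized linear regression (GLM) to model for continuous" values of BP. A logistic GEE on a 5 mm systolic fall from baseline is named beside it. Covariate adjustment is for between-group differences that are observed despite randomisation.
- **Fallback for missed visits** (Data collection): a woman who cannot attend can supply home BP from the loaned monitor.
- **Devices** (Table 2): the office device is used at baseline, 6 and 12 months; the home monitor is used at every time point. The 6-week and 3-month readings are therefore home BP only.

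**The concern.** A regression with 12-month BP as its outcome has nothing to fit for a woman who lacks that value. Unless a further step is added she drops out of the comparison, and so do her earlier readings, which help to predict the missing one. The label promises a comparison of the groups as randomised; the named model delivers it only if the women who remain stand in for those who left.

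That cannot be taken for granted here. The trial is open-label, and one arm has in-hospital sessions, weekly calls for six weeks, a 3-month booster and on-demand support. Contact of that kind can change who stays, and it can do so differently for women whose BP is high. If it does, the arms can differ at 12 months with no true effect, or a true effect can be distorted.

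**Working it through.** **1. The plan's own figures.** 278 × 0.30 = 83.4, so about 83 randomised women would lack a 12-month BP and about 195 (97 per arm) would have one, if the allowance applies equally to the randomised women. The article gives no alpha, power or SD, so 278 cannot be uniquely reproduced. One set that fits is two-sided 5%, 80% power and SD 12.4: n = 2 × (1.960 + 0.842)² × 12.4² / 5² = 96.6, rounded up to 97 per arm; 97 / 0.70 = 138.6, rounded up to 139 per arm, 278 in total. Other sets come close (SD 13 with inflation by 1.3 gives 280).

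**2. What the named methods use.** The GLM of 12-month BP takes no information from a woman without that value. An unweighted GEE is valid only if loss is unrelated to BP given the covariates in the model, so naming it does not settle the matter.

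**3. Can loss be uneven?** Pilot Table 1 has 12-month BP for 13 of 24 intervention women (11/24 = 46% missing) and 16 of 21 usual-care women (5/21 = 24% missing), 29 of 45 overall, with home readings accepted. The difference is 0.458 − 0.238 = 0.220 (Fisher p = 0.21).

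**4. Simple bound.** Let m₁ and m₀ be the missing shares in the intervention and usual-care arms, and let missing women average d mmHg above observed women in both arms. The completers' difference then departs from the full difference by −(m₁ − m₀) × d.

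| m₁, m₀ | d (mmHg, assumed) | shift (mmHg) |
|---|---|---|
| 0.458, 0.238 | 3 | −0.7 |
| 0.458, 0.238 | 5 | −1.1 |
| 0.458, 0.238 | 8 | −1.8 |
| 0.30, 0.30 | any | 0 |

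**5. Simulation.** 139 per arm, no true effect, SDs from Table 1. Assumed: correlation 0.5 to 0.7 between postpartum visits and 0.35 with baseline; loss rising with 6-month systolic BP at log-odds 0.7 per SD; interim BP fully observed. Ranges cover independent runs; a negative sign favours the intervention.

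| Loss pattern | Bias, 12-month regression adjusted for baseline BP | Type I error | Bias using 3- and 6-month BP |
|---|---|---|---|
| about 41% / 19%, related to BP in both arms | −0.7 to −1.0 | 6–9% | about 0 |
| about 30% / 30%, related to BP in one arm only | −0.9 to −1.5 | 8–13% | about 0 |
| alike in both arms | 0 | 5% | 0 |

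With loss unrelated to BP, using the interim readings lowered the standard error by about 3 to 8%.

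**6. Direction and adjustment.** A separate simulation (SD 13, correlation 0.6 between all visits, about 30% loss) made loss depend on 6-month BP differently by arm, with high-BP women lost from usual care. The bias was +0.5 to +0.9 with baseline adjustment and +1.2 to +2.4 without. So the sign depends on the pattern. The unadjusted figure matters because the plan does not commit to including baseline BP.

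**7. Limit of the remedy.** If half of the lost women also lack interim BP, between a quarter and a half of the bias remained. If 85% lack it, about −0.6 of −0.8 mmHg remained, and the precision gain fell to about 0 to 1%.

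**The case against.** The strongest case against runs as follows.

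- **Silence.** A reader might infer that the plan analyses completers only. It does not say so. It states no missing-data method, and imputation is commonly left to an analysis plan, which is not shown here. This stands: the point rests on the model the article names for its primary question, not on the missing detail. Since imputation followed by the planned GLM would also serve, the GLM itself need not be abandoned.
- **The 30%.** A reader might infer that 30% of randomised women cannot have a 12-month BP. The figure is a recruitment allowance attached to all 323 women, including the 45 who are not randomised. Home BP, reminders and adherence tracking will recover some readings. This stands, but the pilot also accepted home BP at 12 months and still had it for only 29 of 45.
- **The pilot.** A reader might infer that the intervention arm will lose more women. With 11/24 against 5/21 the difference is compatible with chance, and the pandemic disrupted follow-up; the note on the 6-month figures says "Data at 6-month time point does not reflect full sample size as in-person visits were limited due to the COVID-19 pandemic". The pilot shows only that uneven loss is possible.
- **GEE.** The article does not say which visits enter the GEE or rule out weighting. That is fair, but the continuous 12-month comparison is still the GLM.
- **Usefulness of interim BP.** In the pilot, BP was missing for 9 of 45 at 3 months, 14 at 6 and 16 at 12, so many lost women may lack interim values too. This stands and limits the gain.

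The statement under Participants and recruitment that data from withdrawn or stopped women will not be analysed is a separate conflict with intent-to-treat. The 83 above concerns loss to follow-up.

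**Conclusion.** The concern holds in a limited form. The article fixes a single-time-point regression as the primary analysis of a trial that measures BP repeatedly and allows for substantial loss. As written, that model leaves out randomised women without a 12-month BP and ignores what is known of them. Under assumed differential patterns the resulting bias is about 0.7 to 1.5 mmHg, or 14 to 30% of the 5 mmHg target (0.7/5 and 1.5/5), with type I error of about 6 to 13% in place of 5%. These figures rest on the assumed correlations, the assumed strength of the link between BP and loss, and adjustment for baseline BP.

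The documents do not support saying that attrition bias follows from 30% loss: with loss alike in both arms and no true effect the bias is zero. Nor do they show that loss will be uneven. The change is worth making because it is cheap and guards against a plausible problem, not because bias has been demonstrated.

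**What to change.** Define the primary analysis as one of all randomised women that uses the interim BP. Two routes serve:

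1. A likelihood-based repeated-measures model with arm, visit, arm-by-visit, baseline BP and site, taking the 12-month arm contrast as the primary result.
2. Multiple imputation, by arm, of the 12-month BP from baseline and interim readings, followed by the planned GLM.

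Either must account for device, because the 6-week and 3-month readings are home BP only. Add one missing-not-at-random sensitivity analysis that shifts the imputed intervention-arm values, for example from 0 to +8 mmHg, until the conclusion changes. Report 12-month BP completeness by arm. Reconcile the sentence on data from withdrawn or stopped women with the all-randomised analysis.

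The cost is plan wording and some extra SAS programming, with no new data or participants. The result then relies on missing at random, which the shift analysis probes. The gains quoted are upper limits and shrink when lost women also lack interim BP.

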### Randomization procedures

After giving birth, all eligible and consenting postpartum individuals who are planning to breastfeed are enrolled in the RCT and randomly allocated by the research assistant to either the control group (usual in-hospital and community postpartum care only) or intervention group (usual in-hospital and community postpartum care plus the BSEI with an assigned lactation specialist). A usual care group as a primary comparison arm is best suited to assess the effectiveness of a behavioral intervention. A central random allocation sequence is computer-generated (via REDCap) stratified by study site, with an allocation ratio of 1:1 using random block sizes of 2, 4 and 6. Allocation is concealed to all research team members until randomization. The research assistant informs the participants of their group allocation immediately after they’ve completed their baseline measures. Although the RCT participants cannot be blinded, data oversight and analysis will be performed by research personnel blinded to group allocation.

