For secondary analyses, the statistical method to compare groups will depend on the distribution of the outcome variables in question. Mediation effects will be assessed using stratified analyses according to pre-defined clinically relevant characteristics such as parity (1 vs. > 1) and gestational age at delivery (34–37 weeks vs. > 37 weeks). Site-specific, sub-group analyses will be performed to know whether there are differences in the study populations. Statistical analysis will be performed using SAS 9.4 version, performed by the biostatistical unit at the primary study site, guided and overseen by the principal investigators.

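### The 12-month BP model draws its covariates from observed imbalances, so adjustment for baseline BP and site is not guaranteed; the 5 mmHg logistic analysis beside it is unranked and its categories are incomplete

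*Protocol article*

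**What the plan says.** All references are to the protocol article.

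- **Endpoint (Study outcomes).** "Our primary study endpoint is average systolic and/or diastolic BP, in mmHg", with 12 months as the primary time point. Baseline values will exist: "Blood pressure data is collected at baseline, 6 weeks, 3 months, 6 months, and 12 months postpartum".
- **Covariate rule (Statistical analysis).** The arms are first compared at baseline: "We will compare baseline characteristics in the experimental study arms to assess randomization effectiveness". The BP models then follow this rule: "We will calculate beta estimates with 95% confidence intervals (CIs) after adjusting for any observed between group differences despite randomization". No criterion for a difference is given and no covariate is named. The time-to-cessation model in the same section does name example covariates.
- **Second BP analysis (Statistical analysis).** Beside the linear model for continuous BP stands "Generalized Estimating Equation (GEE) analyses using logistic regression (reduction of 5 mm in SBP from the baseline vs. no change". The text does not say which of the two decides the primary question.
- **Baseline BP elsewhere.** In a sensitivity analysis, "delta change in BP from baseline will be assessed".
- **Site.** Randomisation is "stratified by study site, with an allocation ratio of 1:1 using random block sizes of 2, 4 and 6". In the analysis, site appears only here: "Site-specific, sub-group analyses will be performed to know whether there are differences in the study populations".

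**The concern.** Baseline BP is the natural predictor of 12-month BP, and site is the factor on which the randomisation was balanced. A primary model would normally contain both whatever the observed balance. Here a covariate enters only if the arms happen to look different on it, by a standard that is left open. Two things are at stake. The first is precision: the gain from a prognostic covariate comes from its correlation with the outcome and exists whether or not the arms are imbalanced, so a rule keyed to imbalance mostly forgoes it. The second is prespecification: with no threshold and no list, two analysts could follow the sentence faithfully and fit different primary models.

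The logistic analysis adds a smaller problem of the same kind. Its two categories do not cover every participant, so someone must later decide where a fall of 1 to 4 mmHg, or a rise, belongs. It is also unranked against the continuous model.

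**Working it through.** **Inputs.**
- Target difference 5 mmHg, 278 randomised, 30% loss (Sample size calculation). Evaluable per arm: 278 × 0.70 / 2 = 97.3.
- SD of 12-month systolic BP: 13 mmHg overall in the pilot (10.1 and 15.3 by arm). SD of baseline systolic BP: 11.3 (Table 1).
- Not given, so assumed: two-sided alpha 0.05, and baseline-to-12-month correlation r between 0.3 and 0.7.

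**The plan's own figure.** The 278 cannot be checked directly, because alpha, power and SD are not stated. With n per arm = 2(1.96 + 0.84)² SD² / 5² and division by 0.7, SD 12.4 and 80% power give 97 per arm, 194 in all and 278 randomised. At the pilot SD of 13 the result is 107 per arm, 214 in all and 306 randomised. So 278 fits an unadjusted comparison with an SD slightly below the pilot's.

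**Power with and without baseline BP.** Adjustment reduces the residual SD to SD × √(1 − r²). Power = Φ(5 / (residual SD × √(2/97.3)) − 1.96). Unadjusted at SD 13: standard error 13 × 0.1434 = 1.864, ratio 2.683, power Φ(0.723) = 76.5%. At r = 0.5: residual SD 11.26, ratio 3.098, power Φ(1.138) = 87.2%.

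| SD | Unadjusted | r = 0.3 | r = 0.5 | r = 0.6 | r = 0.7 |
|---|---|---|---|---|---|
| 12.4 | 80.3% | 83.9% | 90.1% | 94.0% | 97.6% |
| 13 | 76.5% | 80.3% | 87.2% | 91.8% | 96.4% |
| 15.3 | 62.5% | 66.6% | 74.9% | 81.3% | 89.1% |

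At SD 13, the number randomised for 80% power falls from 306 unadjusted to 278 (r = 0.3), 230 (r = 0.5) or 196 (r = 0.6).

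**What an imbalance rule recovers.** Simulation used 5,000 trials per setting, 97 per arm, baseline SD 11.3 and outcome SD 13. Since the article gives no criterion, the rule was taken as: adjust for baseline BP if it differs between arms at p < 0.05.

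| | r = 0.3 | r = 0.5 | r = 0.7 |
|---|---|---|---|
| Power, never adjusted | 75% | 77% | 76% |
| Power, adjusted only if p < 0.05 | 76% | 78% | 78% |
| Power, always adjusted | 79% | 87% | 96% |
| Type I error, adjusted only if p < 0.05 | 5.0% | 4.1% | 3.4% |
| Type I error, smaller p of the two models | 6.5% | 7.4% | 8.0% |

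The fixed models hold about 5%. The mechanical rule is at or below nominal. Only picking the more favourable model goes above it, here with one optional covariate.

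**Site.** With four sites, an assumed between-site SD of about 4 mmHg and r = 0.5, the baseline-adjusted model without site has type I error 3.8% and power 83.8%. With site it has 4.9% and 86.8%. Leaving out the stratum makes the test conservative and costs about 3 points of power.

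**Logistic categories.** The first category is a systolic fall of 5 mm; the second is no change. Falls between 0 and 5 mmHg, and all rises, fit neither on a literal reading.

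**The case against.** The strongest reply is that this is a condensed article. The sentence does not exclude baseline BP or site, and a covariate list is often left to the SAP. That is fair as far as silence goes, and the absence of a list alone would not be a finding. But the article does state a rule, and the rule is driven by the data. An SAP could add baseline BP and site, yet while the sentence stands, the rest of the covariate set is still chosen after seeing the arms compared. The article also says that analysis will be done by personnel blinded to allocation. This limits choosing a model by its direction but does not supply a criterion. Nor is baseline BP ignored: it appears in the change-from-baseline sensitivity analysis and defines the logistic outcome. Neither puts it in the primary model.

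Some stronger readings are tempting and are not supported:

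- *The rule inflates type I error.* Applied mechanically it does not; see the simulation.
- *A baseline gap like the pilot's (127 vs 132) would bias the result by 1.5 to 3 mmHg.* That gap arose in 45 participants. Here its standard error would be about 11.3 × √(2/97) = 1.6 mmHg, so 5 mmHg would be about 3 standard errors and would be adjusted for under the plan's own rule.
- *Pilot change from baseline favoured control (−10 vs −13).* This subtracts means of different participants (24 and 21 at baseline, 13 and 16 at 12 months), and the 12-month values mix home and office readings.
- *The logistic GEE has about half the power it needs.* A single-visit comparison of proportions gives about 45% to 55% at r = 0.3 to 0.5. But GEE is a repeated-measures method and BP is taken at four follow-ups. The article does not fix the visits, so that figure is not this analysis's power.
- *Dichotomising discards the information in the primary outcome.* The continuous model is listed first and kept; the logistic one is an addition.

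**Conclusion.** The concern holds as a matter of efficiency and prespecification. The randomised comparison remains valid. Because the covariates of the primary BP model are set by observed imbalance without a threshold or list, adjustment for baseline BP and site is not assured. At the pilot SD of 13 this forgoes roughly 4, 11 or 15 points of power at correlations of 0.3, 0.5 or 0.6 (76% against 80%, 87% or 92%). An imbalance test recovers at most about 2 of these points. The size depends on the correlation, which the documents do not give; it is modest at 0.3 and large only if baseline BP in the delivery stay predicts 12-month BP well. It also rests on two-sided 0.05 and the full 30% loss. The site effect is smaller and rests on an assumed between-site SD. The logistic analysis needs a rank and a complete definition.

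**What to change.** Replace the imbalance sentence with a fixed primary model: 12-month systolic BP on arm, baseline systolic BP and site, and likewise diastolic BP on arm, baseline diastolic BP and site. Name any further covariate in advance and choose none from observed imbalance; the baseline comparison then stays descriptive. Label the logistic analysis as supportive, define the responder as a fall of at least 5 mmHg against all other outcomes, and state which visits enter the GEE. When the site term is written, reconcile the number of sites: the abstract lists four Montreal hospitals plus Kingston, while Study design and setting lists three plus Kingston.

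The cost is wording only. Baseline BP is already collected and site is already recorded for the randomisation, so no visit, measurement or participant is added. The change should be made before any outcome data are compared by arm.

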**Discussion:**

This study will assess whether an intensive nurse-led behavioral intervention can improve breastfeeding rates and, in turn, postpartum blood pressure – an early marker for atherosclerotic cardiovascular disease. If effective, this form of enhanced breastfeeding support, along with closer BP and metabolic surveillance, can be implemented broadly in individuals lactating after HDP.

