**Fig. 1 Fig1:**
[figure not shown]
Hypothesized mechanism of cardiovascular protection of breastfeeding in women with hypertensive disorders of pregnancy. Conceptual diagram depicting associations between maternal hypertensive disorders of pregnancy and cardiovascular health, and hypothesized mediation by breastfeeding. Photos used in Fig. 1 were downloaded from iStock through a subscribed account. All photos have a Standard License, meaning we have the right to use the photos in perpetuity, and are referenced in Fig. 1

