**Fig. 3 Fig3:**
[figure not shown]
sheMATTERS Study Schemata. Schema of the sheMATTERS randomized behavioral trial design, additional comparison group, and long-term pragmatic cohort

The primary study objective is to assess whether the BSEI will result in lower systolic and/or diastolic BP, or a lower need for antihypertensive therapy at 12 months postpartum. Secondary study objectives are to 1) assess whether the BSEI will result in higher rates of exclusive and any breastfeeding at 6 months, as well as continued breastfeeding to 12 months; 2) assess whether the BSEI will decrease the rate of having metabolic syndrome at 12 months postpartum; 3) explore maternal blood pressure trajectories over time according to ‘dose’ of breastfeeding; 4) evaluate whether those who breastfeed for longer are more likely to engage in other cardiovascular protective behaviors, such as weight reduction, healthy eating, and higher levels of physical activity at 6 and 12 months postpartum; 5) explore the biological and psychosocial determinants of breastfeeding behavior to 12 months postpartum among those with HDP; and 6) collect bio-samples to measure key inflammatory and angiogenic factors from participants who recently had HDP to advance our understanding of the different phenotypes of these individuals and their associated cardio-metabolic risk in the short and long-term.

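### The analysis labelled mediation stratifies on parity and gestational age, which are fixed before randomisation, so it can show effect modification but not mediation

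*Protocol article*

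**What the plan says.** In the protocol article, the secondary-analysis paragraph under Statistical analysis reads "Mediation effects will be assessed using stratified analyses according to pre-defined clinically relevant characteristics such as parity (1 vs. > 1"), and adds "gestational age at delivery (34–37 weeks vs. > 37 weeks") as the second stratifier. No other analysis in the article is called mediation.

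Randomization procedures fixes the order of events: "After giving birth, all eligible and consenting postpartum individuals who are planning to breastfeed are enrolled in the RCT and randomly allocated".

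Elsewhere the article gives mediation a different content. The legend of Fig. 1 describes the relation between hypertensive disorders of pregnancy (HDP) and cardiovascular health, with "hypothesized mediation by breastfeeding". The Discussion paragraph of the Abstract says the study will assess whether the intervention "can improve breastfeeding rates and, in turn, postpartum blood pressure".

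The main analysis paragraph covers the two links of that chain separately. Breastfeeding outcomes are compared between arms, including a time-to-event analysis of exclusive breastfeeding. For the second link, "we will model breastfeeding first as a continuous exposure variable (number of weeks) with systolic BP as the outcome", and "We will also evaluate the dose-response of breastfeeding categories". The weeks-of-breastfeeding model is introduced by reference to the 45 non-breastfeeding, non-randomised participants.

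**The concern.** A mediator lies on the path from treatment to outcome, so treatment must be able to change it. Parity and gestational age at delivery are settled once the child is born, and allocation comes afterwards. Splitting the treatment effect by such a variable shows whether the effect differs between kinds of participant. It does not show how the effect arises.

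Two consequences follow. A difference between parity or gestational-age strata, reported as the plan labels it, could be taken as evidence about mechanism when it is none. And the mechanism question that the Abstract raises, whether a blood pressure effect arises by way of breastfeeding, would have no estimate behind it even though an analysis called mediation had been done.

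**Working it through.** The article states no figure for this analysis, so there is none to reproduce. The check has three parts.

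**1. Order of the variables**

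| Variable | When fixed | Can allocation change it? | Possible role |
|---|---|---|---|
| Parity | At birth, before randomisation | No | Effect modifier |
| Gestational age at delivery | At birth, before randomisation | No | Effect modifier |
| Breastfeeding duration or exclusivity | After randomisation | Yes | Mediator |

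Both planned stratifiers fail the first requirement for a mediator.

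**2. Can the planned split detect mediation?**

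This was tested by an illustrative simulation with 2,000 participants and 400 replicates. All effect sizes and variances are assumptions:
- The total effect on systolic pressure is −5 mmHg.
- The intervention adds 8 weeks of breastfeeding (residual SD 10 weeks).
- The residual SD of blood pressure is 12 mmHg.
- Parity is split 50:50.

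| True state | Effect, stratum 1 | Effect, stratum 2 | Indirect effect with breastfeeding as mediator |
|---|---|---|---|
| Fully mediated by breastfeeding | −4.97 | −5.01 | −5.02 |
| Not mediated at all | −4.98 | −5.01 | −0.01 |

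The stratum effects are the same in both states, so the planned split cannot tell them apart. A model with breastfeeding as mediator can. That model has its own weakness. With no true mediation, but an unmeasured factor that raises breastfeeding by 6 weeks and lowers blood pressure by 3 mmHg per SD, it gave a false indirect effect of −1.03 mmHg.

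**3. Precision if the strata are read as effect modification**

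Inputs:
- 278 randomised 1:1 with 30% loss (Sample size calculation): 278/2 × 0.70 = 97.3, so about 97 per arm.
- SD 13 mmHg. The article gives no planning SD. This is the pilot's pooled 12-month systolic value (Table 1, n = 29, home and office readings mixed), used here as an assumption.
- Equal strata, also an assumption.

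Results:
- Main-effect SE = 13 × √(2/97) = 1.87 mmHg.
- Interaction SE = 13 × √(8/97) = 3.73 mmHg, twice the main-effect SE.
- Difference between strata needed for 80% power (two-sided 5%) = 2.80 × 3.73 ≈ 10.5 mmHg. The trial's target effect is 5 mmHg.

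Over a range of SD:

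| Assumed SD | Interaction SE | Power for a 5 mmHg interaction |
|---|---|---|
| 12 | 3.45 | about 31% |
| 13 | 3.73 | about 27% |
| 15 | 4.31 | about 21% |

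Unequal strata are worse. With a share f in one stratum, the interaction SE is the main-effect SE divided by √(f(1−f)). At an assumed f = 0.2 and SD 13 this is 1.87/0.40 ≈ 4.67 mmHg.

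Reading the strata one at a time does not help. The SE within one stratum is 13 × √(2/48.5) = 2.64 mmHg. For a 5 mmHg effect identical in both strata, power in each is Φ(5/2.64 − 1.96) ≈ 0.47. The chance that exactly one stratum is significant is then 2 × 0.47 × 0.53 ≈ 50%. With no effect at all it is 2 × 0.05 × 0.95 = 9.5%.

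**The case against.** The strongest reply is that this is one wrong word in a secondary analysis. No listed objective or hypothesis asks for an indirect effect. The nearest objective is to "explore maternal blood pressure trajectories over time according to ‘dose’ of breastfeeding", and the main analysis paragraph serves it. Details of a mediation model, or of how strata are compared, would ordinarily sit in a full protocol or analysis plan that is not shown. Much of this stands. The absence of a mediation model from the article is not in itself an error, and neither is its silence on interaction tests. The reply does not remove the sentence that is present: it names a method that cannot deliver what it is said to assess, and an analysis plan that followed it would carry the error forward.

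The Background calls gestational age a likely mediating factor between HDP and infant neurodevelopment, which may be where the term came from. That does not help here. Every participant has HDP, so that path cannot be estimated in this trial, and stratification would not estimate it anyway.

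A reader might infer more than the article supports:
- That the link from breastfeeding to blood pressure goes untested. It does not: blood pressure is modelled on weeks and categories of breastfeeding, and breastfeeding is compared between arms. What is not described is a joint estimate.
- That the breastfeeding regression ignores arm. Its covariates are not listed, so this is unknown.
- That Fig. 1 sets out the chain from intervention to blood pressure. Its legend concerns HDP and cardiovascular health. The intervention chain comes from the Abstract.
- That the strata will be misreported as mechanism. That is a risk created by the label, not something the article states.

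**Conclusion.** The point holds as a mislabelled analysis whose method cannot answer the question its name poses. This follows from the order of events in the article and rests on no numerical assumption. The article examines each link of the proposed chain but describes no estimate of the intervention's effect on blood pressure through breastfeeding. The breastfeeding-to-blood-pressure regression is an observational comparison, introduced because of the non-randomised group, so randomisation does not protect it.

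The precision figures concern the strata as subgroup analyses. They do not bear on whether the label is wrong, and they depend on the assumed SD, 97 evaluable per arm and the split between strata. Over SD 12 to 15 with equal strata, power for a 5 mmHg interaction is about 21% to 31%.

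Importance is moderate. The point limits what the trial may conclude about mechanism, which is part of its stated rationale. It does not touch the primary intention-to-treat comparison.

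**What to change.** **Needed.** Rename the parity and gestational-age analyses as exploratory effect modification. For each factor report the arm-by-factor interaction estimate with its 95% confidence interval, and state that precision is low. Do not draw conclusions from one stratum being significant and the other not.

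**Only if mediation is to be claimed.** Estimate it in randomised participants alone, with breastfeeding duration or exclusivity as mediator and 12-month systolic pressure as outcome. Adjust for baseline systolic pressure, site and baseline confounders that are actually collected. Pre-pregnancy body mass index, for example, is not listed in Table 2, so its availability should be confirmed first. Label the analysis exploratory. State two assumptions: no unmeasured confounding of mediator and outcome, and no such confounder that is itself changed by the intervention. The second deserves attention because the Background suggests that self-efficacy support may also increase engagement in weight loss, exercise and healthy eating. Include a sensitivity analysis for unmeasured confounding.

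**Cost.** A change of wording for the first part. For the second, a modest amount of extra analysis on breastfeeding and blood pressure data that the trial already collects. No change to recruitment, visits or the primary analysis.
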